### Study population

The source population comprises individuals who are undergoing, scheduled to undergo, or have previously undergone latent TB infection (LTBI) testing at the participating hospitals. Eligible participants include those who (1) are scheduled for LTBI testing, (2) have already completed LTBI testing, (3) are currently receiving TB preventive treatment, or (4) have completed TPT within the past two years.

The inclusion and exclusion criteria are summarized in Table 1. The study targets adults aged 19 years or older, encompassing all individuals eligible for LTBI testing and treatment as defined in the “Korean Guidelines for Tuberculosis (fifth edition, 2024)” [4] and the “National Tuberculosis Control Manual (2025)”. This also includes employees working in congregate settings who are mandated to undergo LTBI screening under the TB Prevention Act [5]. Individuals with a history of treatment for active TB disease are excluded from participation.

**Table 1 pone.0350186.t001:** Eligibility criteria for participation in the STEP-TB cohort.

Category	Criteria
Inclusion criteria	1. Aged ≥ 19 years.
	2. Individuals eligible for LTBI testing or treatment who meet one or more of the following conditions: • Contact of a patient with infectious TB. • Person living with HIV. • Receiving or scheduled to receive immunosuppressive therapy. • Planned treatment with TNF antagonists, other biologic agents, or small-molecule inhibitors. • Presence of fibrotic or calcified lesions suggestive of spontaneously healed TB on chest radiograph. • Receiving or scheduled to receive prolonged corticosteroid therapy. • Having autoimmune disease. • Having chronic kidney disease, including those on dialysis. • Having hematologic malignancy or solid tumor. • Having diabetes mellitus. • History of or planned gastrectomy. • Having chronic lung disease (e.g., COPD, asthma, occupational or environmental lung disease). • Confirmed LTBI conversion within the past 2 years. • Healthcare worker. • Personnel working in congregate settings with a high risk of TB transmission (e.g., hospitals, schools) according to the TB Prevention Act. • Individuals considered at high risk for TB infection by local public health authorities (e.g., homeless persons, residents of shelters) under the TB Prevention Act.
	3. Individuals scheduled for LTBI testing, those who have already completed testing with confirmed results, or those diagnosed with LTBI who have initiated, are receiving, or have completed LTBI treatment within 2 years.
	4. Capable of understanding study procedures, voluntarily consenting to participate, and providing written informed consent.
Exclusion criteria	1. Aged < 19 years.
	2. History of treatment for active TB disease.
	3. Any condition deemed inappropriate for participation by the principal investigator.

COPD, chronic obstructive pulmonary disease; HIV, human immunodeficiency virus; LTBI, latent tuberculosis infection; TB, tuberculosis; TNF, tumor necrosis factor

During the study period, when a patient meeting the eligibility criteria is identified, the attending physician will notify the study coordinator or investigator. The investigator will review the patient’s eligibility according to the inclusion and exclusion criteria, provide a thorough explanation of the study objectives, procedures, potential risks, and personal data protection, and obtain written informed consent from those who voluntarily agree to participate. Eligible participants who have provided consent will then be formally enrolled in the study.

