### Study population and analytic framework

After enrollment, all individuals referred for LTBI testing will constitute the source population of the cohort and will be described in terms of baseline characteristics (Table 2). Participants will then be followed according to their LTBI test results and subsequent treatment status (Fig 1). Individuals with negative LTBI test results will be followed to monitor progression to active TB. Among those with positive LTBI test results, participants will be categorized according to whether they receive TPT. Participants receiving TPT will be followed for both adverse events related to TPT and the development of active TB. Participants with positive test results who do not receive TPT will be followed to evaluate the incidence of active TB for comparative assessment.

**Table 2 pone.0350186.t002:** Study populations and outcomes in the cohort.

Study population	Description	Purpose of analysis	Outcomes assessed
All individuals referred for LTBI testing	High-risk population undergoing LTBI testing	Description of source population	Baseline characteristics
LTBI test negative	Participants with negative LTBI test results	Assessment of natural risk of TB among test-negative individuals	Incident active TB
LTBI test positive	Participants with positive LTBI test results	Population eligible for TPT	Stratified analyses according to TPT status
LTBI positive, TPT treated	Participants receiving tuberculosis preventive treatment	Primary safety analysis population	Adverse events related to TPT; Incident active TB
LTBI positive, TPT not treated	Participants with LTBI who do not receive TPT	Comparative assessment of TB risk	Incident active TB

LTBI, latent tuberculosis infection; TB, tuberculosis; TPT, tuberculosis preventive treatment

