### Outcome measures

The primary outcome is adverse events leading to permanent discontinuation of any drugs in the TPT regimen. This outcome will be defined as any clinical or laboratory event occurring during TPT that results in permanent discontinuation of one or more drugs in the prescribed regimen. For example, in patients receiving a 3HR regimen, discontinuation of rifampicin due to adverse events while continuing isoniazid to complete TPT will be considered as meeting the primary outcome.

The secondary outcomes are completion of TPT, the cascade of care for TPT, and the preventive effectiveness of TPT. TPT completion will be defined as completion of the prescribed TPT regimen within the recommended treatment period according to national guidelines. TPT cascade of care will be described by evaluating the proportions of individuals who are eligible for TPT, initiate treatment, and successfully complete treatment. The preventive effectiveness of TPT will be evaluated the incidence of progression to active TB during the follow-up period.

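### The primary safety set is not limited to people enrolled by their first TPT dose, although eligibility admits current users and recent completers, so discontinuation risk and completion are open to selection bias

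*Protocol article*

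**What the plan says.** **Eligibility.** The Study population section gives four routes into the cohort. The last two read "3) are currently receiving TB preventive treatment, or (4) have completed TPT within the past two years". Table 1, inclusion criterion 3, repeats the idea and adds a category: "those diagnosed with LTBI who have initiated, are receiving, or have completed LTBI treatment within 2 years". Both places also admit anyone whose LTBI testing is already done.

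**Analysis set.** In the section on the analytic framework, the split is by treatment only: "Among those with positive LTBI test results, participants will be categorized according to whether they receive TPT". Table 2 describes the treated group as "Participants receiving tuberculosis preventive treatment" and gives its purpose as "Primary safety analysis population". There is no separate class for people whose treatment began or ended before enrolment.

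**Outcomes.** Under Outcome measures, "The primary outcome is adverse events leading to permanent discontinuation of any drugs in the TPT regimen". Dropping one drug of a combination counts: in the 3HR example, "discontinuation of rifampicin due to adverse events while continuing isoniazid to complete TPT will be considered as meeting the primary outcome". Completion is a secondary outcome, and so is the cascade: "TPT cascade of care will be described by evaluating the proportions of individuals who are eligible for TPT, initiate treatment, and successfully complete treatment".

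**Analysis and schedule.** The Statistical analysis section models adverse events as present or absent by logistic regression, with CKD as the exposure, and treats completion similarly. Adverse-event visits are timed from treatment start (Day 14, Day 28, end of treatment), and the final visit is 12 months after initiation. The sample size is stated as 548 TPT initiators.

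**The concern.** Eligibility and outcome are linked. To enter as a current user, a person must not have stopped the whole regimen so far. To enter as a completer, a person must not have stopped it at all. Early discontinuations, which the Day 14 and Day 28 visits are placed to detect, have already been filtered out of these two groups. Completion is certain for anyone admitted because they completed.

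If these people sit in the denominator, three results are affected:

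- the absolute risk of discontinuation for adverse events, which is the safety figure meant to inform national policy;
- the completion proportion and the later steps of the cascade;
- the CKD contrast, which is the primary objective. It is diluted if late enrolees are equally common in both groups and distorted if they are not.

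A logistic model of a yes/no outcome has no entry time, so it cannot correct for late entry. A person who finished treatment up to two years before consent also cannot attend visits timed from the first dose.

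**Working it through.** **Inputs from the protocol (Sample size calculation).** Risks of 20% with CKD and 10% without; 15% of TPT initiators with CKD; two-sided α 0.05; 80% power; 548 initiators, hence 548 × 0.15 ≈ 82 with CKD and 466 without.

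**Assumed input.** f, the share of the set already on or finished with TPT at enrolment. The protocol does not give it; the range used is 10% to 50%.

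**Step 1: the plan's own figure.** The pooled two-proportion formula at 15:85 needs 107 participants with CKD, so 107/0.15 ≈ 714 in total, not 548. With N = 548:

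- pooled risk = (82 × 0.20 + 466 × 0.10)/548 = 0.115
- SE under the null = √[0.115 × 0.885 × (1/82 + 1/466)] = 0.0382
- SE under the alternative = √[0.20 × 0.80/82 + 0.10 × 0.90/466] = 0.0463
- power = Φ[(0.10 − 1.96 × 0.0382)/0.0463] ≈ 0.71

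The gap between 548 and 714 is a separate matter. Here 0.71 serves only as the starting point.

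**Step 2: equal late-enrolee share in both groups, no events among them.** Observed risk = true risk × (1 − f).

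| f | CKD | non-CKD | power at 548 | N for 80% power |
|---|---|---|---|---|
| 0 | 20% | 10% | 0.71 | 714 |
| 10% | 18% | 9% | 0.66 | 807 |
| 20% | 16% | 8% | 0.61 | 920 |
| 30% | 14% | 7% | 0.56 | 1,067 |
| 50% | 10% | 5% | 0.45 | 1,540 |

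**Step 3: relax the zero-event assumption.** If late enrolees carry half the full risk, observed risk = true risk × (1 − f/2). Power is then 0.69 at f = 10% (19% vs 9.5%) and 0.59 at f = 50% (15% vs 7.5%). The loss is smaller but in the same direction.

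**Step 4: share differs by CKD status, no events among late enrolees.** The true odds ratio is (0.20/0.80)/(0.10/0.90) = 2.25.

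- 30% late in CKD, 10% in non-CKD: 14% vs 9%; OR = (0.14/0.86)/(0.09/0.91) = 1.65.
- 10% late in CKD, 30% in non-CKD: 18% vs 7%; OR = (0.18/0.82)/(0.07/0.93) = 2.92.

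**Step 5: completion.** With true completion c and a share f admitted as completers, the observed proportion is c(1 − f) + f. The upward bias is therefore f(1 − c), which is positive whenever c is below 1.

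**The case against.** The strongest reply is that admission to the cohort is not membership of the primary analysis set. Table 2 speaks of people receiving treatment, which does not fit someone who has finished. The follow-up text refers to participants who initiate TPT, and the sample size counts initiators. A reader might therefore infer that an initiator-based analysis inside a broader cohort was meant. That may be the intention, but the protocol does not state it. Current users fit the Table 2 description directly, and completers have no other class to go to.

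A second reply concerns a stronger reading: a reader might infer that every late enrolee is counted as event-free. The protocol does not say so. The primary outcome is tied to events during TPT, not to events after enrolment, whereas incident TB is explicitly limited to the period after enrolment. The adverse-event form records onset dates and action taken, so an earlier event could be entered from records. A completer of 3HR who dropped one drug is an event under the protocol's own example. This stands, and it is why the zero-event rows are an illustration. However, no retrospective collection is described, and recovering past events would not restore the people who were never enrolled because they had stopped.

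Third, a reader might infer that nobody who stopped before enrolment can enter. That is also not supported: the already-tested route, and the word initiated in Table 1, can admit some of them. Their entry is after the fact and depends on who is still attending and willing to consent, so it gives no assurance of balance. It does make the downward bias in risk likely rather than certain.

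Finally, analysis-set detail is often left to the SAP. But the article itself fixes the eligibility routes, the primary safety population and the model, and the problem lies in how these combine.

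**Conclusion.** The point holds in conditional form. As written, the plan admits people selected for not having stopped TPT and does not keep them out of the primary safety population. Unless they are kept out, the adverse-event discontinuation risk is likely biased low and completion biased high. The CKD odds ratio may be biased in either direction if the late-enrolee share differs by CKD status; nothing in the protocol shows whether it does.

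The size cannot be determined from the document. With equal shares of 10% to 50% and no events among late enrolees, power at 548 falls from about 0.71 to between 0.66 and 0.45. If they carry half the full risk, the fall is to between 0.69 and 0.59. The odds ratios of 1.65 and 2.92 show direction only and depend on assumed shares.

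**What to change.** In the analytic framework section and Table 2:

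1. Define the primary safety and completion set as participants who consent on or before the first TPT dose, and count only these toward the 548 TPT initiators.
2. Analyse mid-course enrolees only in a sensitivity analysis with delayed entry at enrolment.
3. Report post-completion enrolees descriptively, outside the adverse-event and completion estimates.
4. In the cascade, report each proportion only for participants enrolled before the step being estimated. Someone tested but not yet treated still contributes to initiation and completion; someone enroled on treatment does not contribute to initiation.

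The work is a few sentences and one derived flag comparing consent date with first-dose date. The cost is that some enrolled participants do not count toward the primary analysis, so reaching 548 may need more recruitment than the planned 1,370, by an amount that depends on the unknown late-enrolee share. The rule should be set before such enrolees accumulate toward the target, because their events before enrolment cannot later be observed prospectively.

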### Study population and analytic framework

After enrollment, all individuals referred for LTBI testing will constitute the source population of the cohort and will be described in terms of baseline characteristics (Table 2). Participants will then be followed according to their LTBI test results and subsequent treatment status (Fig 1). Individuals with negative LTBI test results will be followed to monitor progression to active TB. Among those with positive LTBI test results, participants will be categorized according to whether they receive TPT. Participants receiving TPT will be followed for both adverse events related to TPT and the development of active TB. Participants with positive test results who do not receive TPT will be followed to evaluate the incidence of active TB for comparative assessment.

**Table 2 pone.0350186.t002:** Study populations and outcomes in the cohort.

Study population	Description	Purpose of analysis	Outcomes assessed
All individuals referred for LTBI testing	High-risk population undergoing LTBI testing	Description of source population	Baseline characteristics
LTBI test negative	Participants with negative LTBI test results	Assessment of natural risk of TB among test-negative individuals	Incident active TB
LTBI test positive	Participants with positive LTBI test results	Population eligible for TPT	Stratified analyses according to TPT status
LTBI positive, TPT treated	Participants receiving tuberculosis preventive treatment	Primary safety analysis population	Adverse events related to TPT; Incident active TB
LTBI positive, TPT not treated	Participants with LTBI who do not receive TPT	Comparative assessment of TB risk	Incident active TB

LTBI, latent tuberculosis infection; TB, tuberculosis; TPT, tuberculosis preventive treatment

**Fig 1 pone.0350186.g001:**
[figure not shown]
Study population and analysis framework of the STEP-TB cohort. LTBI, latent tuberculosis infection; TB, tuberculosis; TPT, TB preventive treatment.

### Study procedures

All study procedures will be conducted as part of routine clinical care. LTBI testing will be performed using interferon-gamma release assays (IGRA), and patient management will follow the national TB guidelines according to test results.

The baseline evaluation aims to obtain a comprehensive understanding of each participant’s general health status and social background. Sociodemographic assessment will include economic status, education level, marital status, occupation, smoking and alcohol history. Clinical evaluation will cover current symptoms, medical history, comorbidities, current medications, and vital signs (e.g., blood pressure, heart rate, height, and weight). Laboratory assessment will include LTBI testing, complete blood count, blood chemistry, glycated hemoglobin, fasting glucose, HIV antibody, hepatitis B surface antigen and antibody, and hepatitis C antibody to evaluate baseline health and infection status.

To exclude active TB, additional history taking and diagnostic testing will be performed if necessary. Symptoms suggestive of active TB include persistent cough, sputum production, weight loss, and night sweats. When such symptoms are present, chest radiography will be performed as the initial evaluation. If radiographic findings are indeterminate, the attending physician may perform chest computed tomography for further clarification. Bacteriological testing will also be conducted, including acid-fast bacilli smear and culture, and nucleic acid amplification tests such as Xpert MTB/RIF assay, to confirm or rule out active TB infection.

Participants who initiate TPT will be systematically followed according to the national TB treatment guidelines. The schedule of visits is summarized in Table 3. Clinical evaluations will be performed on Day 14 (Visit 1) and Day 28 (Visit 2) after treatment initiation, and subsequently followed until the end of treatment. The frequency of interim visits during therapy will be determined at the discretion of the treating physician.

**Table 3 pone.0350186.t003:** Study visit schedule and assessments during tuberculosis preventive treatment.

Visit	V0	V1	V2	V3	V4	V5
Visit name	Screening	Baseline	2 weeks	1 month	EOT	EOS
Timing		D0	W1-3	M1-2	M3-10	M11-15
Informed consent	O					
Medical history	O	O	O	O	O	O
TB preventive treatment		O	O	O	O	
Chest imaging		O			O	O
Blood tests		O	O	O	O	
Adherence assessment			O	O	O	
Adverse event assessment			O	O	O	
Blood sampling	O				O	
VAMS sampling			O	O		
Questionnaire		O				

V, visit; D, day; W, Week; M, Month; EOT, End of Treatment; EOS, End of Study; TB, tuberculosis; VAMS, volumetric absorptive microsampling.

To assess the development of incident active TB, an additional follow-up visit will be conducted 12 months after TPT initiation (end of study).

To evaluate drug pharmacokinetics and pharmacogenetic profiles, blood samples will be collected using Volumetric Absorptive Microsampling (VAMS). VAMS collection will be performed at the planned visits (Week 2 and Week 4), precisely 3 hours (±5 minutes) after the participant takes the anti-TB medication. Participants will be instructed to take the medication at a consistent time in the morning before breakfast, and the exact time and date of drug administration and sampling will be recorded in the case report form.

For participants with negative LTBI results, or for those who test positive but do not receive TPT, follow-up assessments will be conducted at 6 months and 12 months after baseline, after which the study will conclude (Table 4). The occurrence of active TB will be evaluated throughout the follow-up period.

**Table 4 pone.0350186.t004:** Study visit schedule and assessments for participants with negative latent tuberculosis infection results or without tuberculosis preventive treatment.

Visit	V0	V1	V3	V4
Visit name	Screening	Baseline	6 months	EOS
Timing	−D14	D0	M3–10	M11–15
Informed consent	O			
Medical history	O	O	O	O
Chest imaging		O	O	O
Questionnaire		O		

V, visit; D, day; W, Week; M, Month; EOT, End of Treatment; EOS, End of Study

Study participation may be discontinued under specific circumstances. Participants who withdraw their informed consent will discontinue further study procedures. Investigator may also discontinue participant’s involvement if, in their clinical judgment, continued participation is deemed inappropriate due to medical, safety, or other relevant considerations. Participants who discontinue study participation will not be excluded from the analysis. Instead, all available data up to the point of discontinuation will be retained and reported where applicable.

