**Methods:**

STEP-TB is a multicenter, prospective observational cohort study conducted at four university-affiliated hospitals in the Republic of Korea. Adults aged ≥19 years who are eligible for latent tuberculosis infection (LTBI) testing or TPT according to national guidelines will be enrolled, including individuals with chronic kidney disease, chronic lung disease, diabetes mellitus, immunosuppressive conditions, malignancy, or occupational risk. LTBI testing will be performed using interferon-gamma release assays, and TPT regimens will follow national guidelines. Participants initiating TPT will be followed for up to 12 months from treatment initiation. Those with negative LTBI results or without TPT will be also followed for up to 12 months. Adverse events, treatment adherence, and completion will be systematically assessed. Blood samples, including volumetric absorptive microsampling, will be collected in a subset of participants for pharmacokinetic and pharmacogenetic analyses.

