### TB preventive treatment

Standard regimens for TPT include short-course rifamycin-based options such as 4 months of daily rifampin (4R) or 3 months of daily isoniazid plus rifampin (3HR) [4]. For individuals at increased risk of drug–drug interactions or adverse events, 9 months of daily isoniazid monotherapy (9H) may be considered as an alternative. If treatment with 9H must be discontinued due to hepatotoxicity or other contraindications, 6 months of isoniazid monotherapy (6H) can be used as a secondary option.

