### Ascertainment of incident active TB during follow-up

The occurrence of active TB during the follow-up period will be assessed through scheduled study visits and telephone follow-up when participants are unable to attend in person. At follow-up visits, participants will undergo clinical evaluation including symptom screening and chest radiography. If active TB is suspected based on symptoms or radiographic findings, additional microbiological testing, including sputum smear microscopy, nucleic acid amplification testing, and mycobacterial culture, will be performed according to standard clinical practice. Incident active TB will be defined as microbiologically confirmed or clinically diagnosed TB occurring after study enrollment during the follow-up period.

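### The TB follow-up clock for treated participants runs from TPT initiation, although people who finished TPT up to two years earlier are eligible, so anyone who completed more than 3 to 9 months before entry (depending on regimen) has no follow-up left at the nominal 12-month visit

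*Protocol article*

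**What the plan says.** **Eligibility.** Study population admits, as its fourth category, people who "have completed TPT within the past two years". Table 1, inclusion criterion 3, repeats this for those diagnosed with LTBI who "have initiated, are receiving, or have completed LTBI treatment within 2 years".

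**Clock for treated participants.** Study procedures, after Table 3, states: "To assess the development of incident active TB, an additional follow-up visit will be conducted 12 months after TPT initiation (end of study"). The Abstract agrees: "Participants initiating TPT will be followed for up to 12 months from treatment initiation". Table 3 gives the end-of-study visit a window of months 11 to 15.

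**Clock for the others.** Under Study procedures and Table 4, test-negative participants and untreated positives are seen at 6 and 12 months after baseline.

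**What counts.** "Incident active TB will be defined as microbiologically confirmed or clinically diagnosed TB occurring after study enrollment during the follow-up period".

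**Use.** Table 2 lists incident active TB as an outcome of the treated group. Outcome measures makes preventive effectiveness, judged by progression to active TB during follow-up, a secondary outcome. Statistical analysis assigns it time-to-event models.

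**The concern.** The eligibility rule and the follow-up rule use different origins. Eligibility looks back up to 24 months from the end of treatment, whereas follow-up looks forward 12 months from its start. For a past completer, part or all of that 12 months has elapsed before consent, and TB during the elapsed part cannot count.

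At stake is the treated side of the preventive-effectiveness comparison. Some members of that group may have no observable risk time, and no scheduled visit or chest image at which TB could be found, while the comparison groups are observed for a year from baseline. How much harm follows depends on how these people are handled in the analysis.

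**Working it through.** **Inputs from the protocol article**
- Nominal regimen length *D* (TB preventive treatment): "4 months of daily rifampin (4R) or 3 months of daily isoniazid plus rifampin (3HR"), "9 months of daily isoniazid monotherapy (9H") and "6 months of isoniazid monotherapy (6H").
- End-of-study clock *C*: 12 months from initiation; latest edge of the Table 3 window, 15 months.
- Months from completion to enrolment *U*: 0 to 24.

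**Step 1: follow-up left at entry.** This is max(0, *C* − *D* − *U*). The most that can be left, for someone enrolled on the day of completion, is *m* = *C* − *D*.

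| | 3HR | 4R | 6H | 9H |
|---|---|---|---|---|
| *m* at month 12 | 12 − 3 = 9 | 12 − 4 = 8 | 12 − 6 = 6 | 12 − 9 = 3 |
| Eligible months with nothing left (24 − *m*) | 15 | 16 | 18 | 21 |
| *m* at month 15 | 12 | 11 | 9 | 6 |

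This step needs no assumption beyond nominal duration. Actual duration moves it a little. The completion windows under Treatment adherence and completion (4 months for 3HR, 6 for 4R, 12 for 9H) would leave 8, 6 and 0 months. Finishing 3HR at 80% of doses without a gap takes 0.8 × 3 = 2.4 months and leaves 9.6.

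**Step 2: share of past completers with nothing left.** The article does not give the distribution of *U*, so three are assumed:
- even over 0–24 months: (24 − *m*)/24
- linearly falling to zero at 24 months (recent completers over-represented): ((24 − *m*)/24)²
- steeper, exponential with rate 1/6 per month, truncated at 24: (e^(−*m*/6) − e^(−4))/(1 − e^(−4))

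For 3HR at month 12 these give 15/24 = 62.5%, (15/24)² = 39.1%, and (0.2231 − 0.0183)/(1 − 0.0183) = 20.9%.

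| Clock, spread | 3HR | 4R | 6H | 9H |
|---|---|---|---|---|
| Month 12, even | 62.5% | 66.7% | 75.0% | 87.5% |
| Month 12, falling | 39.1% | 44.4% | 56.3% | 76.6% |
| Month 12, steep | 20.9% | 25.0% | 35.6% | 59.9% |
| Month 15, even | 50.0% | 54.2% | 62.5% | 75.0% |
| Month 15, falling | 25.0% | 29.3% | 39.1% | 56.3% |

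Under the even spread at month 12, mean follow-up left is *m*²/48: 81/48 = 1.69, 64/48 = 1.33, 36/48 = 0.75 and 9/48 = 0.19 months. The comparison groups have 12.

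**Step 3: what this does to the TB outcome.** Take someone who finished 4R 12 months before entry. Treatment began 4 + 12 = 16 months before entry, so the 12-month point passed 4 months before consent. There are three ways to handle this person:
- *Delayed entry at enrolment:* zero time, no contribution, no bias from this source, but less information.
- *Counted in a proportion as treated without TB:* one more person in the denominator who could not have had an event.
- *Risk time started at TPT initiation:* 12 event-free months are credited. TB in those months could not have counted, because it preceded enrolment. Had it been treated, the exclusion for previous treatment of active TB would have kept the person out.

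The second and third both lower apparent TB occurrence in the treated group.

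**The case against.** **The clock was written for people who start TPT within the study.** The Abstract speaks of participants initiating TPT, and Table 3 runs from consent through day 0, week 2 and month 1. No sentence closes out a past completer by reference to a historical first dose, and a condensed article may leave that schedule to the full protocol. The wording does lean this way. But on this reading past completers have no schedule at all: Table 4 is limited to test-negative or untreated participants, while Table 2 follows the treated group for incident TB. The only clock printed for that group gives some of them no observable time, which is more than an omitted detail.

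**The follow-up is described as up to 12 months from initiation.** True: no treated participant is promised 12 months from enrolment. A reader might infer that no past completer can reach 12 months after entry. That holds at the nominal visit but not strictly at the month-15 edge, where a 3HR user enrolled on about the day of completion could reach it.

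**Most past completers are affected.** A reader might infer this from the even-spread figures. The documents do not support it, because they give no completion dates. For 3HR and 4R, the two standard regimens, the share falls below half once recent completers predominate, and it is exactly 50% for 3HR at month 15 under an even spread.

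**TPT will look more protective.** A reader might infer that this bias is built in. It is not: the planned time-to-event model, coded with delayed entry, would simply give these people no weight. The article does not say they will be counted as event-free.

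**The number of past completers is unknown and the outcome is secondary.** Both stand. The sample size section builds its target from testing candidates who go on to start TPT, so the subgroup may be small.

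**Conclusion.** The eligibility rule and the end-of-study clock conflict and must be reconciled. At the nominal visit, past completers who finished more than 9 (3HR), 8 (4R), 6 (6H) or 3 (9H) months before entry have no TB follow-up left; the rest have at most that many months. This rests only on the stated rules and nominal regimen lengths.

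The proportion affected rests on an assumed spread of completion dates and could be well under half or well over it. The number of people cannot be derived from the article.

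The certain consequence is lost information on preventive effectiveness. Bias in favour of TPT is conditional on counting these people as event-free or starting their risk time at initiation. The primary outcome concerns events during TPT and is not affected by this point. It should be corrected before such entrants accumulate, but it does not threaten the main objective.

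**What to change.** Amend the end-of-study sentence in Study procedures, and Table 3, in one of two ways:

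1. For anyone enrolled after the first TPT dose, start TB risk time at enrolment (delayed entry) and set end of study at 12 months after enrolment. Keep 12 months from initiation for those enrolled by the first dose.
2. State that people who completed TPT before enrolment do not contribute to the TB-incidence analysis.

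**Cost of option 1.** One later contact per late entrant; telephone follow-up is already allowed when a participant cannot attend. The calendar limit is the one untreated participants already face. Recruitment ending in August 2027 plus 12 months is August 2028, within data collection to September 2028. The same section also allows enrolment through December 31, 2027, and 12 months from then is December 2028, which does not fit. That tension exists already for the groups followed from baseline, so the amendment does not create it.

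**Cost of option 2.** Wording only, and a smaller treated group for this outcome.
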